#### Physical activity intervention (ERS)

Participants will undergo a 16-week PA program, consisting of two sessions per week (45–60 min each session). Participants will be asked to perform the activity at a moderate-to-vigorous intensity (according to each individual’s fitness levels) during the main part of each session. Intensity will be estimated using the modified Borg Scale of Perceived Exertion [39] (e.g. moderate-intensity activity will be considered 4–6 and vigorous-intensity activity will be 7–9) or with training loads (i.e. ankle weights and dumbbells) corresponding to 70–80% of one repetition maximum, adjusted progressively during the training period.

The ERS program will be based on a combination of aerobic, strength-based and balance activities. Aerobic training may include walking, rowing, using an elliptical trainer, cycling, fitness/water aerobics, Nordic walking, swimming, dancing and/or any other activity such as games which increase heart rate and respiratory frequency. During the first week, these activities will be performed at a moderate intensity, with bout duration based on each individual aerobic level. Progression will include increasing the duration and/or the intensity (e.g. increasing resistance on the bike ergometer or increasing walking speed on Nordic walking) up to a maximum of 9 of the same Borg Scale. The intervention will be tailored for the participants with a low functional level (score of 4–6 of the SPPB), in which more strength training will be performed.

Lower-body strength exercises will include functional tasks such as rising from a chair, stair climbing, knee bends, floor transfer, walking, lunges, leg squat, leg extension, leg flexion, calf raise, lower back and abdominal curl using ankle weights, elastic bands, training devices (e.g. leg press), free weights or any other material available (e.g. water bottles or sand sacks). Upper-body exercises may include pulldowns, low row, chest press, shoulder press and biceps curl. The first session will be used to calculate the baseline intensity. The first two weeks of the intervention will be used as familiarisation, with the focus on technique of the different exercises. Following the two-week period, training intensity will be individually calculated by the 4–8 repetition maximum method (i.e. maximum number of repetitions to failure between 4 and 8) for each exercise using different training tools devices (e.g. fixed weights machine, free weights, elastic bands) and body weight (e.g. loaded sit-to-stand, squats, lunges). Lower-body exercises will be performed explosively (e.g. as rapid as possible) during the concentric phase of the movement and controlled during the eccentric phase.

Balance-based exercises will focus on functional activities. Balance activities will be designed to challenge the visual (e.g. eyes open/closed), vestibular (e.g. move head) and somatosensory (e.g. stand on foam) systems. Static balance will consist of two-leg and one-leg balance with toes or heels raised and tandem standing with eyes open or closed on different surfaces. When training dynamic balance, activities such as walking on different surfaces, with varied elevations, and performing a dual task (cognitive and functional task such as catching, throwing and reaching), incorporating different gait patterns (e.g. narrow walking, longer strides, zigzag walking) and variations in gait speed, will be performed. Balance exercises will include function-focused activities such as walking with obstacles while wearing standard sunglasses (worn over corrective lenses as needed) to mimic a semi-dark environment, walking while carrying a package that obstructed the view of the feet and walking while picking up objects from the floor. Initially the participants will perform one or two sets of 6–8 repetitions of each exercise; the number of repetitions will be increased when a participant is able to complete eight repetitions showing no difficulty; the maximum number of repetitions will be 20. Three sets of exercises of increasing complexity will be designed; when an easier step will be achieved without assistance, the individual will be asked to perform the next more complex set of exercises.

Participants will be encouraged to report any negative sign or symptom resulting from the exercises during the sessions. A brief summary on the ERS and SMSs interventions can be found in Table 1.

#### ERS + SMS sessions

In order to fully inform the development of the SMSs intervention, a number of preliminary steps were carried out. A systematic review of interventions which aimed to reduce SB in older adults was undertaken to identify the components of these interventions, particularly BCTs. Once these were established, each intervention site conducted focus groups with older adults in order to get their opinions on the proposed BCTs which would be utilised in the SMSs intervention. On completion of both these tasks, and guided by social-cognitive theory, an initial logic model was developed to help determine how different intervention components (i.e. inputs) might have an impact on the proposed study outcomes (e.g. SB, PA, quality of life and functional capacity). The initial SMSs intervention was tested by each intervention site as part of a feasibility study before it was refined for the final SITLESS trial. SMSs training materials were developed and workshops were conducted by each partner to help fully explain the SMSs intervention to the instructors. Monitoring and support for the SMSs instructors is planned on a monthly basis using a mixture of face-to-face meetings and teleconferences.

Participants randomised to this group will take part in a local ERS combined with SMS intervention lasting 30 weeks in total. Both the ERS and SMS sessions will be led by suitably qualified fitness instructors who have been previously trained regarding the SMS intervention. There will be 11 SMS sessions: one taking place before the ERS intervention, seven during the ERS intervention and three after the ERS. BCTs will be used to guide the structure and content of the sessions [40]. These sessions will consist of a one-to-one session, six group-based sessions in local leisure / community centres and four telephone calls to offer additional support to the participants and to find how they are getting on with the SMS intervention. The SMS sessions will be structured as listed below.

One-to-one visit (Familiarisation Stage): the main aims of the one-to-one visit will be to introduce the SMSs intervention and materials to the participant and to start developing a rapport. The participant will be given an information booklet which will give further details on SB and some ideas on how to sit less and be more active (i.e. SITLESS tips). The participant will also be given a Yamax DigiWalker SW-200 pedometer to wear during the course of the SMSs intervention and will be shown how to put this on by the instructor (the participant information booklet will contain instructions on how to use the pedometer). The participant will be given an activity diary to use during the duration of the SMSs intervention to monitor their daily step counts, weekly time in PA / exercise and use of SITLESS tips. This will also allow them to monitor their daily step counts and weekly time in PA / exercise during the first three weeks of the intervention in order to develop baseline readings before the first group-based session. The final task will be to establish long-term functional goals that the participant would like to achieve in the months after completing the intervention. The one-to-one visit is expected to last approximately 50 min.

Six group-based sessions in the local leisure or community centre (Ramping and Maintenance Stages): the main aims of the group-based sessions will be to retrieve the participants’ step counts and weekly time in PA / exercise recorded in their activity diaries and their use of SITLESS tips as well as agreeing on participants’ goals for the following weeks. The participants will be encouraged to gradually increase their daily step counts, weekly time in PA / exercise and their use of the SITLESS tips. Each group-based session will also cover a specific theme such as goal-setting, identifying barriers and facilitators for PA and SB in the neighbourhood and at home, environmental signposting and problem-solving techniques. It is hoped that these sessions will act as an opportunity to improve participants’ motivation and increase the level of social support to sitting less and being more active. Each group-based session is expected to last approximately 45–60 min.

Four telephone calls (Adherence Stage): the main aims of the telephone calls are to provide motivational support and advice to participants to sit less and be more active as well as trying to understand and support participants to maintain their goals (daily step counts, weekly time in PA / exercise and SITLESS tips). Each telephone call is expected to last no more than 20 min.

#### Control group (CG)

Researchers will give to all participants during the first informative meeting (prior assessment) a written general booklet standardised across sites with the WHO recommendation regarding PA regular practice for health. During the intervention, a health advice meeting with standardised topics about healthy lifestyle and feedback on some outcomes will be held twice in the Primary Health Centre (at week 5 and at week 11). Researchers will send a letter or make a phone call prior to the next assessment.

### Outcome assessment

The ERS group will take 16 weeks and the ERS + SMS group will take 30 weeks (including the four phone calls) (see Fig. 1). Assessments will be conducted by the same assessors at the following time points: T0 = baseline pre-intervention, T1 = at month 4 post intervention, T2 = at month 16 (12 months after the end of the intervention), and T3 = at month 22 (18 months after the end of the intervention). (Fig. 2 shows the SPIRIT figure). All researchers in charge of conducting the assessments will undergo a standardised training session.

**Fig. 1 Fig1:**
[figure not shown]
Schedule of SITLESS interventions

**Fig. 2 Fig2:**
[figure not shown]
SPIRIT figure

Personal information regarding age, gender, marital status, living arrangement, educational background, medical conditions, and smoking and alcohol habits will be collected at baseline.

The costs of the interventions (ERS, SMS and the CG intervention) will be also collected by a structured questionnaire.

Primary outcomes of the study include: (1) SB as sitting time and the number of minutes spent in activities requiring ≤ 1.5 MET, as objectively measured by hip worn ActiGraph® accelerometer, and in addition with ActivPal® (used in Barcelona and Ulm) and Axivity® (used in Odense and Belfast) accelerometers worn on the thigh, and as self-reported according to the Patient-centered Assessment and Counseling for Exercise (PACE), Sedentary Behavior Questionnaire); and (2) physical activity as daily CPM and intensity of exercise performed, as measured by ActiGraph®. Primary and secondary measures will be collected at the four time points. For an overview of primary and secondary outcomes, outcome measures, instruments and assessment time points, see Table 2.

**Table 2 Tab2:** Overview of outcomes, outcome measures, instruments and assessment time points

Outcomes	Outcome measures	Instrument	Assessment time point^a^
Personal information	Age, gender, civil status, living arrangement, educational background, medical conditions, and smoking and alcohol habits.	Primary care records Self-report	T0
Primary outcomes			
Sedentary behaviour	Sitting time and the number of minutes spent in activities requiring ≤ 1.5 Metabolic Equivalent Tasks.	Actigraph® ActivPal® Axivity® Sedentary Behavior Questionnaire	T0, T1, T2, T3
Physical activity	Daily counts per minute and intensity of exercise, and daily step counts.	Actigraph®	T0, T1, T2, T3
Secondary outcomes			
Physical function	General function Aerobic capacity Static balance	SPPB 2-minutes’ walk test Unipedal stance	T0, T1, T2, T3
Muscle function	Handgrip strength	Takei analogue Hand Grip Dynamometer	T0, T1, T2, T3
	Mean strength and power with concentric contraction of isoinertial movement performing 3 exercises: (a) 30-s chair stand rise; (b) five repetitions of arm curl with both hands using a 2-kg and 4-kg weight; and (c) four counter-movement jumps.	Linear encoder	
Health economics’ related outcomes	Use of sport services, and use of health and social services, medications, number of falls.	Interview	T0, T1, T2, T3
Anthropometry	Weight, height, body mass index, waist and hip circumference.		T0, T1, T2, T3
Bioimpedance	% fat; % muscle	Tanita BC 420S MA bioimpedance analyser	T0, T1, T2, T3
Blood pressure	Systolic and diastolic blood pressure; heart rate.	OMRON M6 comfort	T0, T1, T2, T3
Activities of Daily Living		6-item questionnaire	T0, T1, T2, T3
Self-rated health and health-related quality of life		SF-12 EUROQOL-5D ICECAP-O	T0, T1, T2, T3
Anxiety		HADS	T0, T1, T2, T3
Depressive symptoms		HADS	T0, T1, T2, T3
Social network		Lubben Social Network Scale-6	T0, T1, T2, T3
Physical activity self-regulation		12-item Physical Activity Self-Regulation Scale	T0, T1, T2, T3
Self-efficacy for exercise		Marcus’s Self-Efficacy Questionnaire	T0, T1, T2, T3
Disability		Short form Late Life Function and Disability Index	T0, T1, T2, T3
Fear of falling		Short Falls Efficacy Scale – International	T0, T1, T2, T3
Loneliness		Short form De Jong Gierveld Loneliness Scale	T0, T1, T2, T3
Executive function		Trail Making Test	T0, T1, T2, T3
Physical fatigue		Pittsburg Fatigability Scale	T0, T1, T2, T3
In a subsample:			
Level of frailty-associated biomarkers and inflammation	IL-6, hsCRP, TNF-alpha, IGF-1.	Blood sample	T0, T1
Sarcopenia-associated markers of muscle quality	Myostatin, IL-6, IL-8, IL-15, VEGF, BDNF, FGF21, irisin, myostatin, Type 2/Type 1 fibre ratio, Wnt and Notch signaling, CDC42	Muscle biopsy	T1

^a^Assessment time points: T0 = baseline pre-intervention, T1 = at month 4 post intervention, T2 = at month 16 (12 months after the end of the intervention), and T3 = at month 22 (18 months after the end of the intervention)

*SPPB* Short Physical Performance Battery, *ICECAP-O* ICEpop CAPability measure for Older people, *HADS* Hospital Anxiety and Depression Scale

### Economic evaluation

The health economic evaluation performed alongside the SITLESS clinical trial will be integral to the main RCT, providing useful guidance upon the cost-effectiveness of the intervention. It will be conducted following NICE [41] recent economics method guidance for the implementation of the cost-effectiveness analysis, as well as CHEERS guidelines for the reporting of the results [42, 43].

Being a population health intervention conducted in a multi-country setting, the health economic evaluation of the SITLESS intervention poses specific additional challenges related to the evaluation of complex public health interventions of this type [44] as well as to the multi-country nature of the intervention.

The costs of providing the ERS enhanced by SMSs (the ‘intervention’ costs) will be identified from a national health service/publicly funded and personal social services perspective alongside potential cost impacts (costs incurred as well as cost savings) including hospitalisations, accident and emergency visits, appointments with health professionals (health visitor, general practitioner contacts) as well as personal social services (i.e. social services and community care).

An economic logic model will be developed to systematically identify all relevant costs and cost savings as well as to identify potential longer term cost impacts. Following a multi-country costing approach, costs will be evaluated using country-specific unit cost estimates weights; furthermore, costs will be translated into a common currency by using the PPP statistic reported by OECD. Unit cost data will be identified from routine country-specific sources: NHS Reference Costs, PSSRU (UK); InEK - Institute for the Hospital Remuneration System (Germany); Health Department of Catalonia (Spain); Danish National Health Register (Denmark) in order to use country-specific price weights. Furthermore, cross-country comparability between data sources will be checked.

As for the outcomes, self-reported health-related quality-adjusted life-years (QALYs) will be obtained using the EQ-5D-5 L EuroQol [45, 46] instrument as well as the newly developed capabilities measure of outcomes for older people, the ICECAP-O instrument [47]. The multinational aspect of the analysis requires the use of country-specific tariffs, which reflect country-specific differences in health perceptions and preferences and might severely affect Cost-Utility analysis [48–50]. When available, country-specific tariffs will be used to evaluate health outcomes.

The within trial analysis will explicitly take the multi-country nature of the SITLESS trial into account, by using appropriate methodologies as suggested by the most recent literature and best practices. The multi-national feature of the SITLESS trial implies a hierarchical structure of the data and unobserved heterogeneity between clusters that needs to be adequately modelled with appropriate statistical and econometric techniques [51, 52]. Following best practice approaches [53–55] a multiple imputation procedure using chained equations (MICE) will be used to impute missing data separately for each arm of the trial.

Within-trial results will be reported and presented as an incremental cost-utility ratio with the joint distribution of cost/utility pairs being represented on the cost-effectiveness plane and with a cost-effectiveness acceptability curve (CEAC) [56].

The within-trial economic evaluation results will be combined with evidence from the literature linking short-term outcomes with longer-term outcomes to produce a long-term cost-effectiveness decision analytic model. A Markov model will be the envisaged analytic tool to evaluate population health interventions and to examine outcomes over an extended period of time and it will be developed alongside Frew et al. [57] and Roux et al. [58]. However, given that such long-term impacts are likely to be reliant on some untestable assumptions, the model will comprise a detailed sensitivity analysis to explore how cost-effectiveness will vary within all realistic ranges of costs and outcomes.

As recommended by the UK’s NICE guidance on economic evaluation of population health interventions an annual population health discount rate of 1.5% will be applied to costs and outcomes.

### Ancillary blood and muscle sub-studies

Two sub-studies will be performed to further elucidate possible mechanistic pathways between SB, PA and our primary and secondary outcomes. Biomarkers will be assessed at baseline and after intervention in blood samples and only after the intervention in muscle biopsies.

#### Subproject A

Subproject A is an analysis of changes in established core blood biomarkers associated with the intervention. This exploratory sub-study will analyse blood samples from 456 participants (95 participants per arm from two interventional sites n = 570, considering 20% loss of follow-up n = 456). Blood will be drawn from participants at baseline (T0) and at T1 to explore whether the intervention modifies established and accessible blood biomarkers (IL-6, hsCRP, TNF-alpha, IGF-1, WBC, RBC, platelets). Irrespective of the study arm, all participants with an improvement in PA will be analysed and compared to those without improvement in PA.

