### Sample size

A sample size of 1338 participants (randomised to one of three groups of 446 participants) will be needed to detect a moderate effect size of 30 daily counts per minute (CPM) in a two-sided test, at a power of 80% and an α of 0.05, a common standard deviation of 139 of the mean and a 24% dropout rate. A change of 30 CPM is considered a measurable moderate effect size in this population, assessed with ActiGraph GT3X+, and 139 is the standard deviation for CPM found in the literature [37]. The present sample size allows estimation of overall efficacy.

Sample size computations were conducted with online software GRANMO (http://www.imim.es/ofertadeserveis/software-public/granmo/; last accessed on 21/7/2014).

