#### Subproject B

Subproject B is an analysis of post-intervention effects on muscle fibres or muscle tissue components in older adults. This exploratory sub-study will analyse muscle tissue from 60 participants to generate hypotheses on potential effects of reducing SB on muscle tissue. The muscle biopsy will be performed at week 21 (after assessing the post-intervention activity level with accelerometers) from a biopsy specialist and biomarkers will be assessed (Myostatin, IL-8, IL-15, VEGF, BDNF, FGF21, irisin, Type 2/Type 1 fibre ratio, Wnt and Notch signalling, CDC42). In this exploratory analysis, the physical activity profile or the sedentary profile from baseline assessment and of the post-intervention period, respectively, will be used as a main exposure marker to be analysed in relationship to the various biomarker measurements. Beside descriptive and summary measures we will use a multivariable analysis approach to quantify the relationship, and simultaneously adjusting for potential confounders such as age, gender and co-morbidities.

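### Subproject A asks whether the intervention modifies blood biomarkers, but the only comparison it states is PA improvers versus non-improvers irrespective of arm, which on its own estimates an association and not an intervention effect

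*Protocol article*

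**What the plan says.** The article states the aim of Subproject A twice, both times in terms of the intervention: "Subproject A is an analysis of changes in established core blood biomarkers associated with the intervention", with blood drawn at T0 and T1 "to explore whether the intervention modifies established and accessible blood biomarkers". The sample is built by arm: "95 participants per arm from two interventional sites n = 570, considering 20% loss of follow-up n = 456".

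One comparison is then described: "Irrespective of the study arm, all participants with an improvement in PA will be analysed and compared to those without improvement in PA". No comparison of biomarkers between randomised arms is stated in that section.

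Two statements set the context. The introduction to the ancillary studies gives a broader purpose: "Two sub-studies will be performed to further elucidate possible mechanistic pathways between SB, PA and our primary and secondary outcomes". Subproject A is also labelled exploratory: "This exploratory sub-study will analyse blood samples from 456 participants".

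**The concern.** The question is causal and about the intervention, and the recruitment supports a randomised answer. The stated comparison instead groups people by something that happens after randomisation and explicitly sets arm aside.

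People whose activity rises over four months differ from those whose activity does not. An intercurrent illness can lower PA and raise hsCRP or IL-6, and recovering health can do the reverse. A difference between improvers and non-improvers can therefore appear when the intervention does nothing to the biomarkers. Conversely, an intervention effect can be diluted or lost, because each improver group mixes all three arms.

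At stake is how the biomarker results can be read. If this is the only analysis done, the sub-study reports an association under an aim worded as an effect.

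**Working it through.** **The plan's own figures.** 95 per arm × 3 arms × 2 sites = 570. 570 × (1 − 0.20) = 456. Both reproduce. 456 / 3 = 152 completers per arm.

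**What a by-arm comparison could detect.** For one pairwise contrast on one marker, two-sided 5%, 80% power, normal approximation:

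- Detectable difference = (1.960 + 0.842) × √(2/152) = 2.802 × 0.1147 = 0.32 SD.
- With Bonferroni for three pairwise contrasts: (2.394 + 0.842) × 0.1147 = 0.37 SD.
- With Bonferroni for seven listed markers × three contrasts = 21 tests: (3.038 + 0.842) × 0.1147 = 0.445 SD.
- Adjusting for the T0 value at an assumed correlation of 0.6 multiplies these by √(1 − 0.36) = 0.8, so 0.32 becomes 0.26 SD.

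These figures ignore clustering.

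**How well improver status tracks arm.** The article's Sample size section gives an effect of 30 CPM and "a common standard deviation of 139 of the mean and a 24% dropout rate". The within-person correlation ρ is not given and is assumed. Improvement is taken as any rise in CPM, and controls are taken to have no mean change, so 50% of them improve. The SD of change is 139 × √(2(1 − ρ)), and the active-arm share of improvers is Φ(30 / SD of change).

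| ρ (assumed) | SD of change (CPM) | Improvers, active arm | Improvers, control |
|---|---|---|---|
| 0.4 | 152 | 58% | 50% |
| 0.6 | 124 | 60% | 50% |
| 0.8 | 88 | 63% | 50% |
| 0.9 | 62 | 69% | 50% |

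**What the two contrasts estimate.** An illustrative simulation (4,000 runs per setting, 152 per arm, two active arms and a control) compared improvers with non-improvers, and one active arm with control. Changes were standardised. The PA effect was 30/139 = 0.216 SD, which corresponds to ρ = 0.5. The biomarker effects and the loadings on a shared unmeasured factor are assumptions.

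| Setting | Improver difference (SD) | Improver test rejects | Arm difference (SD) | Arm test rejects |
|---|---|---|---|---|
| No biomarker effect, no shared factor | 0.00 | 4.9% | 0.00 | 5.2% |
| No biomarker effect, loading 0.3 | 0.14 | 33.6% | 0.00 | 4.8% |
| No biomarker effect, loading 0.5 | 0.40 | 99.1% | 0.00 | 5.0% |
| Biomarker effect 0.3 SD, not through PA change | 0.02 | 5.9% | 0.30 | 74.3% |

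The improver differences can be checked by hand. A loading of 0.3 on both changes gives a correlation of 0.3² = 0.09, and a split near the mean gives 0.09 × 2√(2/π) = 0.14. A loading of 0.5 gives 0.25 × 1.596 = 0.40. In the last row, the active-arm improver share is Φ(0.216) = 0.585. Overall (0.5 + 2 × 0.585)/3 = 0.557 improve. Active-arm members then make up 70.1% of improvers and 62.4% of non-improvers, and 0.3 × (0.701 − 0.624) = 0.02 SD.

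So the improver contrast can signal an intervention effect that is absent, and can miss one that is present. With no shared factor and no effect it behaves correctly, so the problem is what it estimates, not its nominal error rate.

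**The case against.** The strongest reply is that the comparison serves a different, legitimate purpose. The sub-studies are introduced as mechanistic, Subproject A is exploratory, and relating PA change to biomarkers is a reasonable exposure analysis for that purpose. Subproject B does much the same. This stands, and it is why the comparison should be kept, labelled as an association. It does not make the comparison answer the intervention question that Subproject A itself poses.

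A reader might infer that randomisation is discarded and that the sub-study cannot answer its question. The article does not support that. It does not say that the improver comparison is the only analysis. In Table 2 the subsample rows follow the secondary outcomes without a new outcome heading, and the Data and statistical analysis section plans models of change between intervention groups for main and secondary variables. A by-arm analysis of the blood markers could be covered there. It is not clearly covered: that section never names the biomarkers, and its models run from T0 to T3 while blood is taken only at T0 and T1.

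A reader might also fault Subproject A for naming no confounder adjustment, whereas Subproject B plans "simultaneously adjusting for potential confounders such as age, gender and co-morbidities", and for leaving improvement undefined. A condensed article may leave both to the full protocol, so neither is held against the plan.

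The numbers have limits too. The improver shares depend on an assumed correlation and a cut at zero. The 30 CPM effect is a design value, and the article gives no separate month-4 effect. The last simulated setting is extreme for a PA programme, since it has the biomarker effect bypass PA change altogether.

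**Conclusion.** The mismatch is real and lies within one section: an intervention aim and recruitment by arm, with a single stated comparison that ignores arm. Followed as written and alone, it gives an association open to confounding and reverse causation, not an intervention effect. Whether a by-arm analysis is also planned cannot be settled from the article.

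Improver status is only a weak proxy for arm: about 58% to 69% against 50%, under the assumptions above. The simulation shows the direction of the possible errors; its sizes follow from assumed inputs and do not predict this trial.

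The weight is modest. The sub-study is exploratory, and no primary conclusion of the main trial depends on it. The remedy costs little, so the text is worth correcting.

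**What to change.** - Name, as the analysis for the stated aim, the comparison of T1 biomarkers between the three randomised arms, adjusted for the T0 value and site.
- Keep the PA-change comparison as a secondary, exploratory association, irrespective of arm if wished, adjusted for confounders as in Subproject B, and preferably with PA change as a continuous variable.
- If no by-arm analysis is intended, the least that is needed is to reword the aim as an association between PA change and biomarker change.
- If the full protocol already contains the by-arm analysis, say so in this section.

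The cost is wording and a little more analysis work. T0 and T1 samples are already planned in every arm, and the planned 570 recruited and 456 completing stand unchanged.

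### Subproject A compares PA improvers with non-improvers; any such split keeps at most about 64% of the information in the continuous change in PA, so 456 pairs act like about 290 or fewer.

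*Protocol article*

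**What the plan says.** Subproject A of the protocol article has a stated aim, a size and one named comparison.

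- **Aim:** "to explore whether the intervention modifies established and accessible blood biomarkers", with blood drawn at T0 and T1.
- **Size:** "95 participants per arm from two interventional sites n = 570, considering 20% loss of follow-up n = 456".
- **Status:** "This exploratory sub-study will analyse blood samples from 456 participants".
- **Comparison:** "Irrespective of the study arm", "all participants with an improvement in PA will be analysed and compared to those without improvement in PA".

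The article does not define improvement. It gives no cut-off, no rule for confirming a change and no choice of measure. The outcome table (Table 2) lists several PA measures: "Daily counts per minute and intensity of exercise, and daily step counts". The Sample size section supplies the only scale for judging a change in CPM: "A change of 30 CPM is considered a measurable moderate effect size in this population", and "139 is the standard deviation for CPM found in the literature". It does not link either figure to the sub-study.

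**The concern.** Change in PA is continuous and measured with error, and it is to be reduced to two classes. Someone who rises slightly counts the same as someone who rises a great deal, and people near the cut are placed mostly by measurement noise. The sub-study asks whether biomarkers move with activity, so discarding the size of the change discards much of the evidence. The stake is precision: a real association is more likely to be missed although the blood samples and accelerometer data have been collected.

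**Working it through.** **1. The plan's own figure.** 95 participants × 3 arms × 2 sites = 570, and 570 × (1 − 0.20) = 456. Both figures reproduce exactly.

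**2. Information kept by a split.** Assume that the change score is approximately normal and that biomarker change is roughly linear in it with a modest slope. A cut at c standard deviations from the mean, with proportion p above it, keeps the fraction φ(c)² / [p(1 − p)] of the information in the continuous score.

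| Cut (SD from mean) | p above | Fraction kept | × 456 |
|---|---|---|---|
| 0 (median) | 0.500 | 2/π = 0.637 | 290 |
| 0.5 | 0.309 | 0.352² / (0.309 × 0.691) = 0.581 | 265 |
| 1.0 | 0.159 | 0.242² / (0.159 × 0.841) = 0.439 | 200 |

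The median is the best case and every other cut loses more. The bound does not depend on the cut-off chosen or on the T0–T1 correlation.

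**3. Would a minimum change help?** The SD is 139 CPM (Sample size section). The T0–T1 correlation r is not in the documents; 0.6 to 0.9 is assumed. Noise SD of the change = 139 × √(2(1 − r)). With no true change, the chance of an observed rise of at least 30 CPM is 1 − Φ(30 / noise SD).

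| r (assumed) | Noise SD (CPM) | Labelled improver at ≥ 30 CPM with no true change |
|---|---|---|
| 0.6 | 124 | 40% |
| 0.7 | 108 | 39% |
| 0.8 | 88 | 37% |
| 0.9 | 62 | 31% |

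The noise is about two to four times the 30 CPM that the article treats as measurable. A cut-off at 30 CPM therefore changes little.

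**4. What this means for power.** In a simulation under assumed effects, regressing biomarker change on continuous CPM change had power of 46–47% at r = 0.6, against 32–34% for the split. At r = 0.9 it was 89% against 71%. Error under no association stayed at about 5–6%. Step 2 agrees. Power of 89% corresponds to a standardised effect of 1.960 + 1.227 = 3.187; multiplied by √0.637 = 0.798 this is 2.54, and Φ(2.54 − 1.96) is about 72%.

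**5. Which continuous model.** Once baseline CPM is a covariate, the coefficient on change equals the coefficient on T1 CPM given T0 CPM, so it reflects activity level as well as change. This was simulated for a model of the T1 biomarker adjusted for baseline biomarker and baseline CPM. The settings were n = 456, no true change, an assumed true PA–biomarker correlation of −0.2 to −0.3 and biomarker reliability of 0.6 to 0.8. The nominal 5% test rejected in about 6% to 17% of runs. Change on change did not show this inflation.

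**The case against.** **The definition may stand elsewhere.** A responder definition for an exploratory sub-study is commonly left to the full protocol or the analysis plan, and neither is shown. This stands, and the missing threshold is not the point made here. A reader might infer that any rise above zero counts and that one reading per visit decides. On that reading, half of those with no true change would be improvers by symmetry. The article states neither rule.

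**With no true change there is nothing to dilute.** This also stands. Loss of contrast needs a mix of people who change and people who do not, and its size depends on a correlation that the documents do not give.

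**Regression to the mean.** A reader might infer that a chance-low T0 reading biases the biomarker comparison. With no true change and a zero cut, measured T0 activity would differ between the groups by 49 to 99 CPM (r = 0.9 to 0.6). That gap is measurement error only: in simulation, true activity and biomarkers did not differ between the groups. The documents do not support a claim of bias from this source.

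**Continuous change is noisy too.** Correct. Assume arm effects of 0, 30 and 30 CPM (variance 200) and a true-change SD of 30 to 60 CPM within arms. The reliability of observed change is then (900 + 200) / (1,100 + 139² × 0.8) = 0.07 at worst and (3,600 + 200) / (3,800 + 139² × 0.2) = 0.50 at best. Regression recovers what the split loses, not what the accelerometer loses.

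**The loss is a textbook result and the sub-study is exploratory.** Both are true and limit severity. They do not make the split the better choice.

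**Conclusion.** The point holds in a limited form. The improver/non-improver comparison is a stated analysis choice, and it is less efficient than using the same data continuously. At best it keeps about 64% of the information, so 456 pairs act like about 290 or fewer. This rests on an approximately normal change score and a roughly linear relation. The 31% to 40% mislabelling at a 30 CPM cut-off also rests on the assumed correlation of 0.6 to 0.9.

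It would go too far to say that all the planned samples are spent on this split. The sub-study is sized per arm, its aim refers to the intervention, and the Data and statistical analysis section plans between-arm models for secondary variables. Nor do the documents show that group membership is mostly noise, since that depends on inputs they do not give. Severity is low: the sub-study is exploratory and no primary conclusion depends on it.

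**What to change.** In Subproject A, make the main PA–biomarker analysis a linear regression of biomarker change (T1 − T0) on continuous CPM change (T1 − T0), adjusted for site, with the coefficient and its confidence interval reported per 30 CPM. Keep the improver/non-improver split as a descriptive display and base no conclusion on it. Do not use adjustment for baseline CPM as the main model; show it as a sensitivity analysis.

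The change is to wording only and uses the same blood samples and accelerometer data. It has two costs. It assumes an approximately linear relation, which can be checked with a plot or a curved term, and attenuation from accelerometer error remains and should be acknowledged. The analysis also stays observational, because it still relates biomarkers to achieved activity and not to randomised arm.
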